### Exclusion criteria

We will exclude the women who are (1) unable to understand simple verbal commands or do not follow the instructions provided during the assessment; (2) affected by infectious or degenerative diseases; or (3) present III or IV genital prolapse according to the pelvic organ prolapse quantification.

### Non-adherence criteria

We will consider as non-adherence criteria any report of unbearable pain during the gynecological evaluation, more than 20% absences during the intervention period, or those who withdraw their consent to participate in the research.

### Interventions

The researchers will assign the women to one of the three groups: PFMT group, PFMT associated with active intracavitary photobiomodulation group, or PFMT associated with sham intracavitary photobiomodulation group. The exercise program will last 50 min per session, a 5-min warm-up, and a 45-min exercise, including the rest time between them. A total of 24 sessions will be conducted twice a week. Figure 1 illustrates the study flow diagram.

**Figure 1 fig-1:**
[figure not shown]
Flow diagram of the protocol.

There will be four exercise modalities in the PFMT group: (1) warm-up (fast and slow contractions, cough simulations, and plantar flexion associated with pelvic floor muscle contraction in a standing position; (2) pelvic floor muscle and respiratory training; (3) pelvic floor muscle and abdominal training (abdominal transverse muscle contraction associated with arm bridge and bipedal bridge); and (4) pelvic floor muscle training and pelvic mobility. There will be progressions for each modality related to the positioning, starting in dorsal decubitus and progressing to orthostatic or a harder level, such as using a ball to perform a bipedal bridge. There will be two series for the initial 4 weeks and three series for the last 4 weeks. During all the exercise modalities pelvic floor muscle contractions will be required. Figure 2 illustrates the protocol.

**Figure 2 fig-2:**
[figure not shown]
Protocol description illustration. Created in Canva.

The PFMT group associated with photobiomodulation will perform the physical exercise, and right after exercising, the women will use the photobiomodulation device (Fluence Maxx-HTM®, Alpharetta, GA, USA) (Fig. 3). Table 1 demonstrates the LED equipment characteristics and irradiation parameters. The vaginal atrophy protocol will start with 25 J/cm^2^, continuous emission mode, during 450 s. A red, low-intensity light with a wavelength of 660 nm depicts the emission. The protocol is in accordance with previous studies (Lanzafame, de la Torre & Leibaschoff, 2019). The women will be in a lithotomy position during the photobiomodulation intervention. So, a probe covered by a nonlubricated condom but with a lubricant gel, will be inserted in the vaginal canal. Before starting the photobiomodulation intervention, the researcher will wear glasses and request the women to wear them.

**Figure 3 fig-3:**
[figure not shown]
Photobiomodulation device and intracavitary probe.

**Table 1 table-1:** Information about the LED equipment characteristics and irradiation parameters.

LED equipment	Irradiation parameters
Equipment	Fluence Maxx-HTM®
Wavelength (nm)	660 ± 10%
Fluency (J/cm^2^)	0.0555
Total power (W)	4
Treatment time (s)	450
Number of LEDs on probe	12
Intimate applicator area (cm^2^)	72
Irradiation	Intravaginal

The women allocated to the PFMT associated with the sham intracavitary photobiomodulation group will perform the same protocol of the PFMT associated with the active intracavitary photobiomodulation group, except for the intracavitary photobiomodulation that will be off and will not release the red light. As the women will be wearing the protection glasses, they will not realize the absence of the red light.

For all groups, the interventions will be individualized. Furthermore, the women will receive educational content throughout the sessions informing them about menopause, risk factors, location and function of the pelvic floor, types of sexual dysfunctions, types of UI, functioning of the bladder and intestine, and the importance of a healthy lifestyle.

### Outcomes

After the inclusion criteria, the included women will start the first evaluation before interventions. Then, there will be another evaluation after the twelfth and twenty-fourth session (midpoint and final evaluations). Another evaluation will occur 1 month after the end of the interventions (follow-up). The women will answer some questionnaires and perform physical and functional tests related to the pelvic floor muscles in accordance with the published license. Figure 1 illustrates the study flow diagram.

The primary outcome will involve measuring pelvic floor muscle vaginal manometry. The device Peritron, model 9300AV, will evaluate the pelvic floor muscle pressure. Initially, the evaluator will instruct the women to empty their bladder and remain in the lithotomy position. A conical sensor probe introduced in the vaginal canal will capture the pressure generated by the pelvic floor muscle. During the test, the evaluator will instruct the women to perform three maximum pelvic floor muscle contractions without contracting the abdominal, hip adductor, and gluteal muscles. The interval between the contractions will last 30 s. We will calculate the three attempts average and classify them according to the following criteria: very weak (7.5–14.5 cmH_2_O), weak (14.6–26.5 cmH_2_O), moderate (26.6–41.5 cmH_2_O), good (41.6–60.5 cmH_2_O) and strong (>60.6 cmH_2_O) (Angelo et al., 2017).

The international consultation on incontinence questionnaire – short form (ICIQ-SF) will evaluate UI; the female sexual function index (FSFI) will evaluate sexual function; the Utian Quality of Life (UQOL) scale will evaluate quality of life; the patient global impression of improvement (PGI-I) will evaluate the perception of improvement; the modified oxford scale will evaluate pelvic muscle strength; and the vaginal health index (VHI) scale will analyze vaginal atrophy. They will feature as secondary outcomes in the study’s evaluation.

The ICIQ-SF is a self-administered questionnaire that classifies urinary loss. The questionnaire is translated and validated in the Portuguese language (Tamanini et al., 2004). It presents four questions that evaluate the frequency, severity, and impact of UI on quality of life. It also presents a set of eight self-diagnostic items that allow evaluation of UI causes or situations experienced by patients. Only the first three questions will be scored and the total score will range from 0 to 21 points. The impact on quality of life will be classified as no impact (0 points); light impact (1 to 3 points); moderate (4 to 6 points); severe (7 to 9 points), and very severe (10 or more points) (Tamanini et al., 2004).

The FSFI is a self-administered questionnaire validated in the Portuguese language and Brazilian population. It presents nineteen questions about sexual activity during the last 4 weeks, involving six domains: desire, excitation, lubrication, orgasms, satisfaction, and discomfort/pain. The total score requires the domain’s sum. Scores below 26.55 points will classify as sexual dysfunction (Thiel Rdo et al., 2008).

The UQOL scale evaluates the quality of life, specifically for menopausal women. It is validated and adapted for Brazilian women and presents 23 questions divided into four domains: occupational, health, emotional, and sexual. The score spans from 23 to 115, with a higher score indicating a better quality of life (Utian et al., 2002; Lisboa et al., 2015).

The PGI-I is a simple and easy-to-use scale that presents clinical applicability to the perception of the intervention. It presents a single question about urinary functioning compared to the period before intervention. The score ranges from 1 (very much better) to 7 (very much worse) (Yalcin & Bump, 2003).

The modified Oxford scale evaluates the pelvic floor muscle through a manual palpation to measure the pelvic floor muscle strength. The scale presents six points to quantify the pelvic floor muscle strength according to the following criteria: grade 0: no contraction; grade 1: small and no sustained contraction; grade 2: low intensity and sustained contraction; grade 3: moderated contraction, feeling the intravaginal pressure compressing the evaluator’s finger; grade 4: satisfactory contraction, the evaluator’s fingers are compressed by the intravaginal pressure; grade 5: strong contraction, the evaluator’s fingers are compressed towards to pubic symphysis (Da Roza et al., 2013).

The VHI scale evaluates vaginal atrophy by assessing the vaginal humidity, vaginal liquid volume, vaginal elasticity, pH, and vaginal epithelium integrity. Values below 15 indicates that vaginal mucosa is atrophic. To evaluate the pH, we will position a universal pH tape (MERCK**®** (MColorpHastTM, Merck, Rahway, NJ, USA) in the right vaginal wall during 1 min without contact with the cervix or cervical mucus. A pH below and above five indicates normal and atrophy vaginal trophism, respectively (Bachmann & Nevadunsky, 2000). All the instruments that will measure the outcomes of the study are in accordance with the published license. Figure 4 illustrates the evaluation process.

**Figure 4 fig-4:**
[figure not shown]
Evaluation process.

### Participants timeline

Initially, the included women will provide the information requested in the evaluation form, questionnaires, Oxford Modified Scale, vaginal manometry, vaginal health index, and vaginal pH. The midpoint evaluation will occur immediately after the twelfth session. The final evaluation will be conducted immediately after the twenty-fourth intervention. Another evaluation will take place 1 month after the last intervention (follow-up). The evaluations will follow the same protocol by a blinded evaluator. See the SPIRIT diagram (Fig. 5).

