Considering these assumptions, photobiomodulation has been utilized to prevent muscle damage, repair muscle tissues, improve muscle performance, and reduce fatigue (Xu et al., 2018; Toma et al., 2016; Ferraresi et al., 2015; Lanferdini, Krüger & Baroni, 2018). Moreover, the chronic use of photobiomodulation associated with strength exercise training potentiates the strengths generated by the exercise (Ferraresi, Huang & Hamblin, 2016; Vanin et al., 2016; Baroni et al., 2014; Ferraresi et al., 2011). Evidence demonstrates that the photobiomodulation intervention before or after an 8-week muscular training potentiated the muscular thickness and strength (Ferraresi, Huang & Hamblin, 2016; Vanin et al., 2016; Baroni et al., 2014; Ferraresi et al., 2011; Vassão et al., 2018). The therapeutic effects generated by photobiomodulation have been associated with improvements in fatigue reduction, post-exercise recovery, and muscular performance (Baroni et al., 2014; Ferraresi et al., 2011; Miranda et al., 2016).

Although pelvic floor alterations, such as urinary and sexual dysfunctions do not threaten women’s lives, they generate significant limitations (Levine, Williams & Hartmann, 2008). In this sense, urinary and sexual dysfunctions impose physical, social, and occupational restrictions, affecting the women’s quality of life (Levine, Williams & Hartmann, 2008). Therefore, it is important to investigate the effects of innovative therapies to treat the dysfunctions generated by the GSM in order to improve women’s health and quality of life.

Considering the photobiomodulation physiological effects on the pelvic floor muscle and the scarcity of clinical trials related to this subject, this preliminary study aims to explore the feasibility and therapeutic window for PFMT isolated and associated with photobiomodulation in women affected by GSM who present urinary and sexual dysfunctions.

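### The final evaluation follows straight after a training session, so manometry cannot separate lasting training gain from the acute post-session state, which may differ between arms

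*Protocol article*

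**What the plan says.** The Participants timeline section sets both on-treatment evaluations directly after a session: "The midpoint evaluation will occur immediately after the twelfth session" and "The final evaluation will be conducted immediately after the twenty-fourth intervention". A blinded evaluator repeats the same measurements each time. For baseline, the Outcomes section says "the included women will start the first evaluation before interventions". Follow-up comes one month after the last intervention.

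Under Interventions, each session has 50 minutes of exercise, and every modality requires pelvic floor contractions. In the photobiomodulation arm, "right after exercising, the women will use the photobiomodulation device", for 450 s, and "a probe covered by a nonlubricated condom but with a lubricant gel, will be inserted in the vaginal canal". Sham women go through the same procedure with the device off. No probe or gel is described for the arm that only trains.

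The primary outcome is the mean of three maximum pelvic floor contractions on manometry. The vaginal health index (VHI) works by "assessing the vaginal humidity, vaginal liquid volume, vaginal elasticity, pH" and epithelial integrity. The Introduction describes the effects of photobiomodulation as "associated with improvements in fatigue reduction, post-exercise recovery, and muscular performance".

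The Statistical analysis section lists baseline, the reading after the last intervention, and the 1-month reading. The midpoint is not among them. The article mentions no rest interval and no removal of gel before testing.

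**The concern.** The reading that closes the treatment period is taken under different conditions from the readings it is compared with. The muscle group that has just been exercised is tested at maximum effort, while baseline and 1-month readings carry no such load.

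If the acute state were the same in every arm, this would mainly affect change within an arm. The article gives two reasons why it may not be the same:

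- The active arm has just received light, which the Introduction links to less fatigue and better recovery. Sham cannot remove an acute effect of light, because light is exactly what differs between the two arms.
- Both probe arms have a device period between exercise and testing. The training-only arm has none, so recovery time is unequal even if light does nothing.

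A third route concerns secondary outcomes. Three of the five VHI items (humidity, fluid volume, pH) are scored after gel has been used in two of the three arms.

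At stake is what a difference at the final evaluation means: strength built over the programme, or the state of the muscle minutes after the last session. No later analysis can split the two at that time point.

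**Working it through.** **1. What comes before each reading (read as the same visit)**

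| Reading | Training only | Sham | Active |
|---|---|---|---|
| Baseline | nothing | nothing | nothing |
| Final | 50 min exercise | 50 min exercise, 450 s probe, gel | 50 min exercise, 450 s probe, gel, light |
| 1 month | nothing | nothing | nothing |

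Across the final row:

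- Active versus sham differs in light only; gel and device time are balanced.
- Each probe arm versus training only differs in gel and in 450/60 = 7.5 min of device time. The active arm also differs in light.
- Exercise is common to all arms. On an additive scale, fatigue common to all arms cancels in the group-by-time interaction.

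**2. The plan's own figure**

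The Sample size section gives f = 0.23, 80% power, alpha 5% and a total of 42, for a repeated-measures within-between interaction. Number of measurements, correlation and sphericity are not stated. Assume k = 3 groups, m = 3 times, ρ = 0.5, ε = 1:

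- λ = f²·N·m/(1−ρ) = 0.0529 × 42 × 3/0.5 = 13.33
- df1 = (k−1)(m−1) = 4; df2 = (N−k)(m−1) = 78
- power = 0.822, and 42 is the smallest multiple of 3 that reaches 80%.

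The figure reproduces under these assumptions, and the timing issue does not change it.

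**3. Illustrative size of a differential shift**

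Every input here is an assumption; none is in the article: mean 30 cmH2O, SD 15, acute fall of 10% to 20%, half of it offset by light.

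- 30 × 0.10 × 0.5 = 1.5 cmH2O; 1.5/15 = 0.10 SD
- 30 × 0.20 × 0.5 = 3.0 cmH2O; 3.0/15 = 0.20 SD

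To compare with f = 0.23, a pattern must be assumed. If one arm alone departs at one of three times, f = (2/9)δ, so δ = 0.23 × 9/2 = 1.035 SD. If the arms are evenly spaced at that time, f = δ/√27, so δ is about 1.2 SD. The assumed shift is then roughly 8% to 19% of the effect planned for.

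**4. Consequence for a pairwise test**

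Assume no lasting difference, 42/3 = 14 women per arm, and a two-sided 5% z-test. The standard error is √(2/14) = 0.378 SD unadjusted, or √(0.75 × 2/14) = 0.327 SD with baseline adjustment at ρ = 0.5. The rejection rate is Φ(d/SE − 1.96) + Φ(−d/SE − 1.96).

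| Shift d (SD) | Unadjusted | Baseline-adjusted |
|---|---|---|
| 0.1 | 5.8% | 6.1% |
| 0.2 | 8.3% | 9.4% |
| 0.5 | 26% | 33% |

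The last row lies outside the illustrated range and shows sensitivity only. The planned Bonferroni correction would lower all of these rates.

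**The case against.** The strongest reply is that neither the direction nor the size of an acute effect is documented. The Introduction speaks of associations, gives no time scale, and places them next to statements about chronic use and 8-week training. A reader might infer that the primary endpoint is shown to favour the active arm. The article does not support that; nothing in it says that 450 s of light restores maximum contraction within minutes. This part of the objection stands in full.

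Several further points also stand:

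- Fatigue common to all arms cancels between groups. Within an arm it would understate the gain, not inflate it.
- A reader might take all VHI and pH comparisons to be contaminated. Gel is balanced between active and sham, so only contrasts with training only and change from baseline within the probe arms are exposed. These are secondary outcomes. The timeline also lists palpation and manometry before VHI and pH. If that is the running order, every arm has intravaginal contact first, and whether those steps use lubricant is not stated.
- A reader might infer that gel residue or a longer session unblinds the evaluator. At most it could show that a probe was used, not whether it was active, and nothing says that the evaluator observes the session.
- The midpoint reading is not in the stated analysis, so it carries little weight.

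Finally, the Outcomes section says only that evaluations come after the twelfth and twenty-fourth sessions, and the figures on evaluation and schedule are not available. A separate visit may be intended. That limits the point but does not remove it, because the Participants timeline section states the immediate timing in plain words, and on that wording the final reading is a post-exercise one.

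**Conclusion.** The point holds as a problem of separability, not as a demonstrated bias. If the final evaluation is at the same visit as the last session, the main post-treatment manometry reading combines training gain with an acute state. That state may differ between active and sham through light, and between the probe arms and training only through the device period. VHI humidity, fluid volume and pH may be affected by gel outside the active-versus-sham contrast.

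The only size that can be offered, 0.1 to 0.2 SD and a pairwise error rate of about 6% to 9% in place of 5%, rests entirely on assumed values. The sample size of 42 is unaffected. The 1-month reading is analysed and avoids both the exercise and the gel problem, so the trial keeps one clean comparison. Severity is moderate: a cheap improvement to make before data collection, since the final reading cannot be repaired afterwards.

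**What to change.** In the Participants timeline section, replace the immediate timing of the final evaluation with a separate assessment visit in one fixed window after the last session, identical for all arms (for example 2 to 7 days), with no study exercise, light or gel that day. Do the midpoint evaluation at the next scheduled visit, before that session starts. Word the Outcomes section to match. If a separate visit is already intended, one clarifying sentence closes the point.

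The abstract counts 16 sessions and the Methods 24. These must be reconciled in any case, so that the last session is defined.

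The cost is at most one extra visit per woman, so at most 42 visits, each one more occasion on which a reading can be missed. The midpoint change needs no extra visit, and no staff or procedures are added.

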**Figure 5 fig-5:**
[figure not shown]
SPIRIT flow diagram.

### Sample size

G-Power software version 3.1.9.2 calculated the sample size, according to the ANOVA F test repeated measures, within-between interaction, based on a previous study (Bezerra et al., 2020). We considered the data from the manometry results between groups after interventions. To calculate, we will consider a power of 80%, an alfa error of 5%, and an effect size of 0.23. Therefore, a total of forty-two individuals will participate in the study.

### Recruitment

The women will be recruited at the urogynecology outpatient clinic located in the Maternity Hospital Januário Cicco School from the Federal University of Rio Grande do Norte, Natal, Brazil. The contact with the women will be through doctor referral, written disclosure, and personal contact.

### Randomization, allocation concealment, and blinding

A numeric sequence generated by the software (https://www.random.org/) will randomize the women to allocate (1:1:1) three groups: PFMT group, PFMT associated with intracavitary photobiomodulation group, or PFMT associated with intracavitary photobiomodulation sham group. Each woman will present the same probability to allocate any group. An independent investigator who will not be involved in the evaluation and intervention process will perform it. The women and researchers involved in the assessments and interventions will be blinded.

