## Methods

### Study setting

It is a randomized, controlled, double-blind clinical trial protocol study that will be performed at the urogynecology outpatient clinic located in the Maternity Hospital Januário Cicco School from the Federal University of Rio Grande do Norte, Natal, Brazil, in 2024.

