This protocol presents some limitations and strengths that must be acknowledged. There will be no sensor to confirm if the women are performing efficient pelvic floor muscle contractions during interventions. However, the researcher will stimulate the pelvic floor contraction during the whole session. Also, we will use validated, easy-to-use, and cheap instruments with clinical applicability to evaluate the effects of the treatments. Lastly, a long-term follow-up could demonstrate if the effects of the intervention would last longer.

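### The trial is described as double-blind with women and treating staff blinded, but the arm without a device rules this out: at most, women are blinded between active and sham light

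*Protocol article*

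**What the plan says.** In the Protocol article, Study setting describes the design as follows: "It is a randomized, controlled, double-blind clinical trial protocol study". The Abstract uses the same label. Randomization, allocation concealment, and blinding adds that "The women and researchers involved in the assessments and interventions will be blinded". Neither place limits this to particular arms. Participants timeline states separately: "The evaluations will follow the same protocol by a blinded evaluator".

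The Interventions section gives the content of the arms:

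- **PFMT only:** "There will be four exercise modalities in the PFMT group". All four are exercises, and no probe or sham procedure is described.
- **PFMT plus active light:** "right after exercising, the women will use the photobiomodulation device". The woman lies in lithotomy and a probe "will be inserted in the vaginal canal"; the treatment time is 450 s.
- **PFMT plus sham:** the same procedure, "except for the intracavitary photobiomodulation that will be off and will not release the red light". The text argues that the women will not notice because they wear protective glasses.

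Statistical analysis uses time, group and their interaction, with Bonferroni-corrected post-hoc comparisons. The Conclusion states the expected result as PFMT plus photobiomodulation doing better than PFMT alone.

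**The concern.** A blinding statement tells the reader which comparisons are protected from expectation and from differences in how staff treat participants. Here it covers all three arms, although one arm differs visibly from the other two. A reader would take every between-group comparison as double-blind.

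This bears on what the trial can conclude. Active versus PFMT-only combines any effect of light with the effects of having a probe inserted, of the extra device period and of knowing that one receives a device. Only active versus sham separates out the light. The outcomes are not immune to expectation: manometry records maximal contractions made on instruction, and the ICIQ-SF, FSFI, UQOL and PGI-I record the women's own reports or perceptions. Staff behaviour matters too, since the Discussion says that "the researcher will stimulate the pelvic floor contraction during the whole session".

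**Working it through.** **1. Who can be blinded to what.** Setting the blinding sentence beside the arm descriptions:

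| Contrast | Women | Person delivering the session | Outcome assessor |
|---|---|---|---|
| Active vs sham | Can be blinded (glasses) | No masking described | Stated blinded |
| Active vs PFMT-only | Not blinded to probe vs no probe | Not blinded to probe vs no probe | Stated blinded |
| Sham vs PFMT-only | Not blinded to probe vs no probe | Not blinded to probe vs no probe | Stated blinded |

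Participants are told the aims and procedures of the research (Ethics and dissemination), so a woman who is never offered a probe can infer her arm. At 1:1:1 that is 42/3 = 14 women. The 28 women in the probe arms know that they have a device, but need not know whether it emits light. For staff, seeing whether a probe is inserted is enough to make the sentence untrue.

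**2. The plan's sample size and the test it belongs to.**

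Inputs from Sample size: repeated-measures ANOVA, within-between interaction; effect size 0.23 (taken as Cohen's f); alpha 0.05; power 80%; N = 42. From Randomization: k = 3 groups. From Statistical analysis: m = 3 time points. Assumed because not stated: correlation ρ = 0.5 between repeated measures, and sphericity (ε = 1).

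Formula: λ = f²·N·m/(1 − ρ), df1 = (k − 1)(m − 1), df2 = (N − k)(m − 1); power is the upper tail of the noncentral F beyond the critical value.

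- λ = 0.0529 × 42 × 3 / 0.5 = 13.33; df = 4 and 78; **power 0.82**.
- The smallest N reaching 80% is 41, or 42 with equal arms. The plan's figure reproduces, as a figure for the three-arm omnibus interaction.

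**3. The same calculation for active versus sham only (14 vs 14).**

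k = 2, N = 28, with f held at 0.23:

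- λ = 0.0529 × 28 × 3 / 0.5 = 8.89; df = 2 and 52.
- At alpha 0.05: **power 0.74**.
- At alpha 0.05/3 = 0.0167 (Bonferroni over three pairs): **power 0.57**.

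**4. Sensitivity to the assumed correlation (m = 3).**

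| ρ | Three arms, N = 42 | Active vs sham, alpha 0.05 | Active vs sham, alpha 0.0167 |
|---|---|---|---|
| 0.4 | 0.74 | 0.65 | 0.48 |
| 0.5 | 0.82 | 0.74 | 0.57 |
| 0.6 | 0.91 | 0.83 | 0.69 |

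Counting the midpoint visit (m = 4, ρ = 0.5) gives 0.81 and 0.67 for active versus sham, but Statistical analysis does not list that visit. Holding f at 0.23 for two arms is a further assumption, because the f of a three-group pattern need not be the f of any one pair.

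**The case against.** The case on the other side has several parts, and some of it stands.

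- **Assessor blinding is provided.** Manometry is an instrument reading, averaged over three attempts and taken by a blinded evaluator. This stands: it can hold in all three arms, and the point does not dispute it. It does not remove the woman's own expectation from a voluntary effort or from a questionnaire.
- **Operator knowledge of active versus sham.** A reader might infer that the operator knows the sham status because the device is off. The documents do not go that far. No sentence says who switches the device, the researcher also wears glasses, and a full protocol may describe the masking. What can be said is that none is described here.
- **Device operator and exercise coach.** A reader might assume they are the same person. The text says only the researcher in each place, so this is not established.
- **Size of the bias.** A placebo or attention effect of 0.2 to 0.4 SD might be suggested for the self-reported scales. Nothing in the documents supports a value, and none is offered for manometry. Treatment is individual and education is given in every arm, so the added contact is essentially the device period.
- **Primary contrast.** A reader might fault the article for naming none. That is commonly left to the statistical analysis plan, which is not shown, and the study calls itself preliminary. The planned comparisons also already yield active versus sham. The absence is therefore no fault here; the recommendation on which contrast carries the claim concerns interpretation.

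None of this rescues the blinding sentence. It is a positive statement that the arm descriptions contradict, not a detail lost in condensation.

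**Conclusion.** The contradiction is real and follows from the text alone. The blinding statement cannot hold for the 14 PFMT-only women, nor for staff with respect to probe versus no probe, and two of three pairwise contrasts are not participant-blinded. For active versus sham, blinding of the women is plausible and operator masking is undescribed; that is not evidence that operators are unblinded there. Assessor blinding is unaffected.

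The direction and size of any resulting bias cannot be given from the documents. The consequence is for interpretation: the benefit as framed in the Conclusion is measured on a contrast that the double-blind label does not cover. The power figures (0.82 for the omnibus test; 0.74, or 0.57 with Bonferroni, for active versus sham) rest on f = 0.23 in both settings, m = 3, ρ = 0.5 and sphericity, with no dropout. They show the cost of relying on active versus sham. They are not an error in the stated 42.

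**What to change.** 1. Replace the blinding sentence with one that says: outcome assessors are blinded in all arms; participants are blinded only between active and sham; interventionists are not blinded to PFMT-only versus the probe arms. For active versus sham, either describe how the person at the device is masked or say that this person is not.
2. Qualify double-blind to match in the Abstract and Study setting.
3. Base any claim that photobiomodulation itself adds to PFMT on active versus sham. Label contrasts with PFMT-only, including the one in the Conclusion, as supportive and not participant-blinded.
4. State that the 80% power at N = 42 refers to the three-arm interaction, and give the power for active versus sham with its assumptions.

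The changes are to wording, with two real costs. The blinding label becomes less favourable. The contrast that carries the claim about light is openly shown to fall below 80% power under the assumptions above. The sponsor can accept and state that, which fits a study described as preliminary, or resize.
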